#### Baseline interview

Baseline investigations will be carried out in all the participated six primary hospitals. The contents of the investigations include four aspects, namely socio-demographic parameters, clinical parameters, process indicators and costs on diabetes as shown in Table 2. Data collectors are responsible to guide enrolled patients to finish the baseline investigations. The information of body weight, height, waistline and blood pressure will be measured and recorded in the clinic by the data collector. The Glucose and lipid files will be measured by lab tests. Data of patient socio-demographic parameters, process indicators and costs on diabetes will be provided by the patients or their guardians.

**Table 2 Tab2:** Services to be provided by pharmacists in the primary hospitals

Pharmacists’ services	Details	Methods
Diabetes education	□ Disease introduction □ Control target of blood glucose □ The types and principles of hypoglycemic agents □ Self-monitoring of blood glucose	□ Educate patients of diabetes management in the collaborative clinic. The knowledge will be printed out and given to patients for home study
Medication guidance	□ The importance of medication adherence □ Administration methods(oral & injection medication) □ Administration timing □ The injection technique of insulin □ Drug-drug interaction □ Drug storage	□ Create a WeChat group with all the enrolled patients in, and pharmacists will share diabetes knowledge periodically
Lifestyle intervention	□ Exercise □ Diet	□ Educate patients in the collaborative clinic □ Help patients make a healthy lifestyle plan
ADR * & complications identification and treatment	□ Recognition and prevention of hypoglycemia □ Identification and processing of complications of diabetes □ Identification and processing of ADR	□ Educate patients in the collaborative clinic □ Call the pharmacist if an emergency event occurs

*PS*: *ADR* Adverse drug reaction

#### Randomization and allocation concealment

The randomization protocol was used to select six out of 18 primary hospitals in Hunan province to carry out the study by using a standard protocol available in the website (http://stattrek.com/statistics/random-number-generator.aspx). There will be three centers in each group (intervention group and control group).

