## Methods/design

### Study design

The study is a multi-site randomized controlled trial. We will carry out the study in six primary hospitals in Hunan province. Eligible patients will be randomly assigned to the intervention group (physician-pharmacist collaborative clinics) or the control group (usual care clinics led by a physician) and will be followed up at the 3rd, 6th, 9th and 12th month. Comparison between the two groups will be conducted by assessing the clinical parameters, process indicators and costs on diabetes. Fig. 1 describes the study design.

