### Study settings

Currently in Hunan province, county hospitals, township health centers, and village clinics are the major primary health care providers in rural areas. As there are limited pharmacists and their main responsibility is dispensing in village clinics and township health centers, we chose county hospitals as the research sites. Since there are several county hospitals in each county, we selected the best one in that county as our studied primary hospital with the aim of homogenizing the quality of the settings. We divided these counties into three subgroups based on their per capita income levels, namely high, medium and low incomes counties. We sent invitation letters to 27 primary hospitals and 18 agreed to participated in the study. Finally, we randomly selected six of them (two in each subgroup) to conduct the study as shown in Fig. 2.

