### Procedures

#### Training pharmacists and data collectors

Three pharmacists from the primary hospitals assigned to the intervention group will be trained for three months in the Second Xiangya Hospital. The training courses mainly include two aspects, namely diabetes management and cooperative skills, as shown in Table 1. These pharmacists are required to spend most of their training time either in the outpatient clinic of endocrinology or in the wards of endocrinology to get as much experience as possible. Besides the traditional teaching methods, problem-based learning and scenario simulation learning methods will be implemented to train the pharmacists. Serial tests will be carried out to examine how well the knowledge and skills they have mastered.

**Table 1 Tab1:** Training courses for pharmacists from primary hospitals

Training courses	Details	time
Diabetes management	1.Theoretical knowledge □ Basic knowledge of diabetes, including identification of diabetes complications □ Basic knowledge of hypoglycemic a gents(oral & injection medicine) □ treatment target of blood glucose level □ Laboratory tests interpretation □ Medication adherence □ Diet □ Exercise □ lifestyle 2. Practice and Application in patients 3. Six tests to assess their theoretical knowledge and practice skills	Two months
Cooperative skills	1. Theoretical knowledge on communication skills 2. Practice in outpatient clinics and inpatient wards	One month

Six nurses from each of the primary hospitals will be enrolled as data collectors and will be trained for two weeks in the Second Xiangya Hospital. They will be simply introduced about the background of the project, namely diabetes management and pharmacotherapy. These data collectors will get detailed training of patient enrollment talk, informed consent signature and data collection for assessments. Data collectors will be trained to finish both the printed and the electronic CRF (case report form) forms for assessments.

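### The protocol says patients are randomly assigned, but whole hospitals form the arms and the only random draw described picks hospitals into the study

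*Protocol article*

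**What the plan says.** Under Study design, the protocol article states "The study is a multi-site randomized controlled trial" and continues: "Eligible patients will be randomly assigned to the intervention group (physician-pharmacist collaborative clinics) or the control group". The unit named there is the patient.

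The section Randomization and allocation concealment has two sentences. The first reports a random-number draw: "The randomization protocol was used to select six out of 18 primary hospitals in Hunan province to carry out the study". The second reads "There will be three centers in each group (intervention group and control group"), and gives no mechanism.

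Study settings describes the same draw in more detail. On the counties it says "We divided these counties into three subgroups based on their per capita income levels, namely high, medium and low incomes counties", and of the 18 hospitals that agreed to take part, "we randomly selected six of them (two in each subgroup) to conduct the study".

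The section on training refers to hospitals, not patients, as belonging to an arm: "Three pharmacists from the primary hospitals assigned to the intervention group will be trained for three months".

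**The concern.** Random sampling of sites and random assignment to arms do different jobs. Sampling six of 18 hospitals helps the results generalize to the hospitals that volunteered. It does nothing to make the two arms comparable. The section that should say how the arms were formed reports the first and leaves out the second, while Study design claims random assignment of a unit, the patient, that the rest of the design does not assign.

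The causal reading of the trial is at stake. With three whole hospitals per arm, any difference between the two sets of hospitals is mixed with the effect of the clinic unless chance decided which hospital went where. The title, abstract and Discussion all present a randomized trial, and the Discussion draws policy implications from it. County income is an obvious candidate for such a difference: the authors stratified on it when choosing sites, and their Discussion links lower socioeconomic status among rural patients to less awareness of adherence, lifestyle and glucose monitoring.

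**Working it through.** **Step 1. Which unit goes into an arm?** The relevant sections of the protocol article, side by side:

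- Study design: patients are randomly assigned.
- Training pharmacists and data collectors: hospitals are assigned to the intervention group, and their pharmacists are trained.
- Randomization and allocation concealment: three centers per group.
- Physician-pharmacist collaborative diabetes clinics: three such clinics are set up.
- Usual care clinics: the control group has no pharmacist.
- Recruitment and withdrawn: the steps run from identification by the physician, through explanation and consent, to the baseline form. No allocation step appears.

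The last five agree with each other and not with the first. A patient's arm is fixed by the hospital attended, so patient-level random assignment is claimed but is not a property of this design.

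**Step 2. What is drawn at random?** Study settings and the randomization section both describe one draw, of six hospitals from 18, with two per income level. Its result is a list of sites. No section describes a second draw from those six sites to the two arms.

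**Step 3. The plan's own counts.** Three income levels × 2 hospitals = 6 hospitals. At the target of 100 patients per hospital (Sample size determination), 6 × 100 = 600, which matches the Abstract. Three hospitals per arm give 3 × 100 = 300 patients per arm. These figures are consistent.

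**Step 4. How much could the income pairs matter?** This step assumes an unrestricted random 3 v 3 split, which the article does not describe.

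- Possible splits: C(6,3) = 20.
- Splits with one hospital of each income level in each arm: 2 × 2 × 2 = 8, so 8/20 = 40%.
- Remaining splits: 20 − 8 = 12, so 12/20 = 60%. Direct count: 3 choices of the level with both hospitals in the intervention arm, × 2 choices of the level that supplies the third hospital, × 2 hospitals within that level = 12.

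Each of the 12 has a 2-1-0 against 0-1-2 pattern across income levels. At 100 patients per hospital that is 200/100/0 patients in one arm and 0/100/200 in the other. At the expected 80 to 120 per hospital, the 200 becomes 160 to 240 and the 100 becomes 80 to 120.

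**Step 5. How the figure depends on the assumption.** Under a draw within income pairs, the chance of imbalance in income level is 0%. Under an unrestricted draw it is 60%. If the split was not a random draw, no such probability applies.

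**The case against.** The strongest reply is that the article is silent, and silence is not evidence of a non-random split. Study design does assert random assignment, and the training section speaks of hospitals being assigned. A hospital-level draw may have been made and simply not reported. Figures 1 and 2 were not available for this review; either could show which hospitals are in which arm and whether each income pair was split. Two hospitals at each of three levels, with three per arm, is just what a paired allocation would need. All of this stands, and it limits what can be concluded.

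A reader might go further and infer that the trial is not randomized, that the income pairing was ignored, or that the intervention hospitals were those best able to release a pharmacist for three months. The documents support none of these. The three-month training is a pharmacist eligibility requirement, and the article applies it to hospitals already placed in the intervention group; it does not say that availability decided the arm. Nor is 60% an estimate of the imbalance in this trial, because no unrestricted draw is described.

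The reply that a journal article condenses the full protocol does not dispose of the point. The dedicated section does not abbreviate the allocation method; it reports another random step in its place. The contradiction with Study design over the unit is also on the page and does not depend on anything left out.

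**Conclusion.** The point holds as a contradiction and as a gap in what is described. The statement that patients are randomly assigned is wrong for this design: hospitals form the arms, three against three. The only random step described selects sites, so as described neither patients nor hospitals are randomly assigned to arms. Use of the income pairs for allocation is not stated.

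Whether the hospitals were in fact randomized cannot be settled from the article. If they were, by an unrestricted draw, there was a 60% chance (12 of 20) of an unbalanced income level; if within pairs, none. If they were not, the claim of a randomized comparison is unsupported. The matter needs correction because it decides what the trial can conclude.

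**What to change.** 1. In Study design, state that hospitals are the unit of assignment and that patients follow their hospital.
2. In Randomization and allocation concealment, keep the site draw, label it as site selection, and add how the three hospitals per arm were assigned and whether this was done within income levels.
3. If assignment is still open, assign one hospital of each income pair to each arm by random draw. This is probably no longer possible: Trial status says recruitment began in May 2021, the recruitment window is six months plus at most one, and the article appeared in March 2022.
4. If the split was not random, describe the study as a non-randomized controlled comparison of hospitals and limit the causal conclusion to match.

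The analysis cannot substitute for this disclosure. Adjustment for the baseline value is already part of the primary outcome definition. Adding patients' annual income, which Table 3 already collects, is at most a partial mitigation, because it does not remove confounding at hospital level.

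The cost is wording, plus three random draws if these are still possible; no extra patients or sites are needed. Pairing has a price of its own. With 8 possible allocations, the smallest two-sided hospital-level permutation p-value is 2/8 = 0.25, against 2/20 = 0.10 for an unrestricted split. Neither reaches 0.05, so the choice should be made for balance and the reason stated.

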### Intervention protocol

#### Physician-pharmacist collaborative diabetes clinics

Three physician-pharmacist collaborative diabetes clinics will be established after the pharmacists get comprehensive training. Pharmacists in the collaborative clinics will provide several services which mainly consist of four aspects, including diabetes education, medication guidance, lifestyle intervention, and identification and treatment of adverse drug reaction and complications, as shown in Table 2.

Three measures will be taken to make sure that the project will be carried out smoothly in the collaborative clinics. 1) In the first week, a pharmacist from the Second Xiangya Hospital will stay in the collaborative clinic, monitor the trained local pharmacist and data collector’s work, and give him/her guidance to run the collaborative clinic well. 2) A pharmacist from the Second Xiangya Hospital will periodically go to the primary hospitals and check the progress of the project. Every week, there will be an internet meeting consisting of the PI, main participants and the pharmacists from the intervention group to report the process of the project, describe the problems they meet and exchange their experience in the collaborative clinics. 3) Data collectors are required to entry and upload the electronic CRF forms to the Second Xiangya Hospital within two days when they have finished the printed forms. A separate research staff will carefully check the data and immediately inform the data collectors to amend the errors once occur.

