#### Usual care clinics

Similar to physicians in the collaborative clinics, physicians in the usual care clinics will provide routine services, mainly including diagnosis and treatment without education due to limited time. No pharmacists will be involved in the control group. Data collectors will present in the clinic to enroll patients and collect data of the assessments the same as in the collaborative clinics.

In order to ensure the implementation of the project in the usual care clinics, three measures will be taken: 1) In the first week, a pharmacist from the Second Xiangya Hospital will stay in the clinic and monitor the data collector’s work. A participant from the Second Xiangya Hospital will periodically go to the primary hospitals and check the progress of the project. 2) Every two weeks, an internet meeting consisting of the PI, main participants and the data collectors will be held to monitor the process of the project. 3) Same as the intervention group, data collectors are required to entry and upload the electronic CRF forms to the Second Xiangya Hospital within two days.

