### Data analyses

The sample size was calculated by using the PowerSampleSize program (Vanderbilt University). The data will be analyzed using the SPSS software package (Statistical Package for the Social Sciences), version 22.0 for Windows (SPSS Inc., Chicago, Illinois, USA). Data will be checked for normal distribution by means of the Kolmogorov–Smirnov's test. Values are presented as mean ± standard deviation or median (range) for parametrically or nonparametrically distributed variables, respectively. In compliance with the distribution of data, Student's t-test or Mann–Whitney's U-test will be used for comparisons between the two groups. Chi-square or Fisher's exact tests will be used to compare between the groups with respect to categorical data. The follow-up assessment data will be analyzed using Generalized Linear Mixed Model and survival analysis. *P* < 0.05 is considered statistically significant. All tests are two tailed.

For cost-effectiveness analysis, we will collect the direct and indirect costs of each enrolled patient with T2DM, evaluate their quality of life through EQ-5D-3L utility value from data provided by patients, calculate quality-adjusted life years (QALYs), and analyze the effects of multiple variables by the Linear Mixed Effects Model. Based on this model, the differences between the average costs and the results will be analyzed during the 12 months. The incremental cost effectiveness (ICER) will be calculated, and the univariate and multivariate analyses will be performed.

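### Whole hospitals form the arms, three per arm, but the plan calls it patient randomisation and names between-group tests and a sample size that carry no hospital term

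*Protocol article*

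**What the plan says.** All references are to the protocol article.

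- Study design puts allocation at patient level: "Eligible patients will be randomly assigned to the intervention group (physician-pharmacist collaborative clinics) or the control group".
- Randomization and allocation concealment describes a random-number tool used to pick six of 18 hospitals, then states: "There will be three centers in each group (intervention group and control group". It describes no patient-level sequence and does not say how the six were divided between arms.
- Training pharmacists and data collectors: "Three pharmacists from the primary hospitals assigned to the intervention group will be trained for three months".
- Physician-pharmacist collaborative diabetes clinics: "Three physician-pharmacist collaborative diabetes clinics will be established after the pharmacists get comprehensive training".
- Usual care clinics: "No pharmacists will be involved in the control group".
- Data analyses: "Student's t-test or Mann–Whitney's U-test will be used for comparisons between the two groups", and "Chi-square or Fisher's exact tests will be used to compare between the groups with respect to categorical data". The same section names a generalized linear mixed model and survival analysis for follow-up data, and a linear mixed effects model in the cost-effectiveness analysis. No hospital effect is mentioned for any of them.
- Sample size determination gives 36 patients per group for an HbA1c difference of 0.76% with SD 1.0%, two-sided alpha 0.05 and 90% power. With 10% dropout this becomes 40, which is then set as a minimum for each hospital. The enrolment target is 100 per hospital.

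**The concern.** A hospital either has a trained pharmacist and a collaborative clinic or has neither, so a patient's arm follows from the hospital attended. The recruitment section agrees with this: it goes from consent straight to the baseline form with no allocation step.

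Patients in one hospital share physicians, laboratory, local population and, in the intervention arm, that hospital's pharmacist service. Their outcomes are therefore likely to be correlated. A test that treats about 600 patients as independent counts ordinary differences between three hospitals and three others as evidence about the clinic model. At stake are the false-positive rate and the stated precision of a trial meant to inform rural diabetes policy.

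**Working it through.** **Unit of allocation.** One sentence, in Study design, says patients are assigned. Four sections (randomisation, training, collaborative clinics, usual care) describe hospitals as the arms. The statements conflict, and the operational ones all point to the hospital.

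**The plan's own sample size.** n per group = 2 × [(1.960 + 1.282) × 1.0 / 0.76]² = 36.4, which matches the stated 36 to within rounding. With dropout, 36 / 0.90 = 40. This is the formula for independent patients. No design effect enters.

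**Type I error when patients are treated as independent.** Inputs:

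- Three hospitals per arm (randomisation section).
- m = 90 evaluable patients per hospital (target 100 less 10% dropout).
- Intracluster correlation (ICC): not given in the protocol, so 0.01 to 0.10 is assumed.

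Formulas: design effect DE = 1 + (m − 1) × ICC, and true type I error = 2 × [1 − Φ(1.96 / √DE)].

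| ICC | DE | SE understated by √DE | True type I error |
|---|---|---|---|
| 0.01 | 1 + 89 × 0.01 = 1.89 | 1.4 | 15% |
| 0.02 | 2.78 | 1.7 | 24% |
| 0.05 | 5.45 | 2.3 | 40% |
| 0.10 | 9.90 | 3.1 | 53% |

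Simulation of three against three hospitals (4,000 runs) gave 15%, 23.5%, 39.5% and 53.6% for the patient-level t-test. A t-test on the six hospital means gave 5% to 6%. With 100 patients per hospital the formula gives 17%, 26%, 42% and 55%, and 11% at an ICC of only 0.005. Larger hospital samples make the inflation worse. A mixed model with only a patient effect has the same weakness for the 12-month contrast, because it still treats patients of one hospital as independent of each other.

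**Cost of a hospital-level analysis.** SE of the difference = SD × √[2 × DE / (3m)]; 95% half-width = t × SE, with t = 2.776 on 4 df. Power for 0.76% comes from the noncentral t distribution. With m = 100 and SD 1.0, the patient-level half-width is 1.96 × √(2/300) = 0.16 HbA1c points.

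| ICC | DE | Half-width, 4 df | Power, 4 df |
|---|---|---|---|
| 0.01 | 1.99 | 0.32 | over 99% |
| 0.02 | 2.98 | 0.39 | 97.5% |
| 0.05 | 5.95 | 0.55 | 81% |
| 0.10 | 10.90 | 0.75 | 57% |

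**Degrees of freedom.** Six hospitals less two arm means leaves 4 df. Study settings says two hospitals came from each of three income strata. If each stratum gave one hospital to each arm and the pairs are analysed as such, three differences less one mean leaves 2 df. The protocol does not say which applies.

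**The case against.** The strongest reply is that the primary outcome is defined as adjusted for its baseline value, which an unadjusted t-test cannot do. The mixed model is assigned to follow-up data, so it is probably the main outcome analysis, and the two-group tests may serve baseline comparisons only. A journal article need not list random effects, and a hospital intercept could be in a plan not shown.

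Much of this stands. A reader might infer that the mixed model leaves hospital out; the protocol does not say so. The error rates above therefore apply only if outcomes are compared at patient level or with a patient effect alone. What remains is in the text: the section names patient-level tests for comparing the groups without confining them to baseline, the sample size is individual-level, and the unit of allocation is contradicted.

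Three other stronger readings are not supported.

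- *Hospital differences will appear as a significant effect.* They can. The chance depends on an ICC the protocol does not give. Baseline adjustment may lower it, as may choosing the best hospital in each county to make settings alike.
- *The trial is cluster-randomised.* Only the selection of hospitals is described as random, not the split into arms.
- *The trial is underpowered.* On 4 df, power for 0.76% is about 81% or more for ICCs up to 0.05.

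**Conclusion.** The point holds in this form: the protocol contradicts itself on what is allocated, leaves the assignment of hospitals to arms undescribed, and names between-group tests and a sample size that do not fit allocation by hospital. Patient-level comparison of outcomes would raise a nominal 5% error rate to about 15% to 53% for ICCs of 0.01 to 0.10.

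That size rests on an assumed ICC, on 90 evaluable patients in each hospital, and on no hospital term being used. The harm is to error rate and precision more than to power, unless the ICC is near 0.10 or the analysis is paired on 2 df. It needs correcting before analysis, because the stated two-group tests are invalid for outcomes under the allocation the protocol itself describes.

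**What to change.** 1. Reconcile Study design with the randomisation, training and clinic sections. State how the six hospitals were assigned to arms, and whether one per arm was taken within each income stratum. Describe the trial as cluster-allocated, or as cluster-randomised if that assignment was random.
2. For primary, secondary and cost outcomes, replace patient-level between-arm tests with either (a) a comparison of the six baseline-adjusted hospital means, or (b) a mixed model with a random hospital intercept, plus a patient effect for repeated visits, and small-sample degrees of freedom. Use 4 df if unmatched and 2 df if hospitals are analysed as pairs within income strata.
3. Restate the sample-size section with an assumed ICC range and the resulting power.

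The cost is wording in the design, analysis and sample-size sections. Intervals will be wider, and stated power for 0.76% falls to about 81% at ICC 0.05 and 57% at 0.10 on 4 df. A paired analysis on 2 df would have less power unless matching removes enough between-hospital variance. No further enrolment is needed, and nothing changes for patients.
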